## Ethical considerations:

Ethics approval from the UCSF committee on human research institutional review board and SFVAMC will be obtained prior to commencement of the study. Written, informed consent, will be obtained by all patients prior to trial enrollment. E-cigarettes are a widely available commercial product that are often marketed and used as a means for current smokers to quit smoking[^41^](#_ENREF_41). Recently, the FDA has issued a proposed rule that would extend the agency’s tobacco authority to cover additional products that meet the legal definition of a tobacco product, such as e-cigarettes; however, currently, e-cigarettes are not an FDA-approved form of nicotine replacement therapy (<http://www.fda.gov/newsevents/publichealthfocus/ucm172906.htm>; accessed 9/22/2014). The use of e-cigarettes may be associated with harms greater than those of NRT. These risks will be told verbally and in written format to potential study participants. The largest randomized trial to date (657 participants) investigating e-cigarettes versus nicotine patches did not find an increased adverse event rate in the e-cigarette group, indicating that short-term use of e-cigarettes is likely safe, although the adverse event rate may differ in the veteran population[^10^](#_ENREF_10). Furthermore, there is variability in the quality of commercially available products and the most-studied brand of e-cigarette is not widely available in the USA. We have therefore chosen to study a brand that has at least some published experimental and safety data.

Currently, smokers presenting for surgery receive brief pre-operative advice, but no other intervention regarding smoking cessation. Thus, even if e-cigarettes are not more beneficial than NRT, both arms of the study are receiving care that is likely better than the current standard, due to the incorporation of counselling in both the control and intervention groups.

## Statistical analysis plan:

Descriptive statistics to assess feasibility:

-proportion ineligible for inclusion (95% CI by bionmial exact) and reasons for exclusion

-proportion of eligible veterans declining to participate (95% CI by binomial exact)

Baseline characteristics to be collected prior to randomization: age, gender, race/ethnicity, comorbidities (hypertension, coronary artery disease, chronic obstructive pulmonary disease, diabetes mellitus, other cardiac disease), scheduled surgical procedure and subspecialty, smoking habits (number of cigarettes per day, years smoking), Fagerstrom score for nicotine dependence. Operative day information to be collected in addition to outcomes listed below: surgical procedure, duration of surgery, anesthesia type (local/monitored anesthesia care/regional/general/combined)

| **Outcome** | **Data Description** | **Likely Distribution** | **Hypothesis Test** |
| --- | --- | --- | --- |
| Smoking cessation (primary outcome) | Proportion | n/a | Fisher’s exact test |
| Smoking reduction | Proportion | n/a | Fisher’s exact test |
| Smoking amount | Cigarettes/day, Continuous  Median (IQR) | Normal or skewed (plot histogram) | Normal: two-sided t-test  Skewed:Wilcoxon rank-sum |
| Unanticipated hospital admission | Proportion | n/a | Fisher’s Exact Test |
| Hospital length of stay | Days  Continuous  Median (IQR) | Skewed | Time-to-event using Cox proportional hazards model; graph Kaplan-Meier plot |
| 8-weeks after randomization: Agreement to (0-7 likert) "I was satisfied with product I was given (e-cigarette or patch) to help me quit" (and similar questions regarding how helpful they found it, and whether they would recommend e-cig/patch) | Likert 0-7, Ordinal, Median (IQR) | Skewed | Wilcoxon rank-sum |
| 8-weeks after randomization: During the 6-weeks after you entered the study, how often did you use the product you were given (e-cigarettes or patch)?  Everyday, most days, a few times a week, once a week, less than once a week, did not use at all | Proportion that used everyday Proportion that did not use at all. | n/a | Fisher’s exact test |
| Change in FEV1, FVC, salivary cotinine | Liters, Continuous (Mean, SD) | Normal | Paired t-test |
| Composite of 30-day postoperative complications and mortality | Proportion | n/a | Fisher’s Exact Test |
| Duration in PACU | Hours  Continuous  Median (IQR) | Skewed | Time-to-event using Cox proportional hazards model; graph Kaplan-Meier plot |

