## Sample size estimation:

Previous perioperative studies have shown an absolute difference in smoking cessation rates between intervention and control groups to be 13-76%, with quit rates in the control groups ranging from 4-65%[^4-7^](#_ENREF_4). The proposed sample size is 30 (20 intervention, 10 control), balancing cost against precision, as is conventional for a pilot study. We realize that since the sample size is small, between-group differences may not be statistically significant. However, the proposed sample size will provide rough estimates of Aim 1 (smoking cessation) and Aim 4 (postoperative complications) treatment effects, residuals, and within-subject correlations needed for the full-scale trial. The sample size will also establish the acceptability of the intervention (Aim 2). In order to proceed with a full trial assigning ENDD use to a larger number of veterans, we would like to determine from this pilot study if ENDD is more acceptable to patients than NRT, as reported in previous qualitative studies[^11^](#_ENREF_11). The proposed sample size will have 80% power to detect an effect size of 1.085, accepting an alpha of 0.05 and assuming the standard deviation of a likert scale (0-7) of satisfaction with the intervention (ENDD or NRT) is around 1.0[^37^](#_ENREF_37). Even if we are underpowered to see smaller differences, the point estimates and confidence intervals will provide rough estimates that will be useful in planning a future study.

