## Randomization and blinding:

After collection of baseline data, randomization will be done by computer-generated scheme with randomly permuted block sizes of 3 or 6 in a 2:1 fashion. Allocation will be concealed by consecutively numbered, sealed, opaque envelopes. Due to the nature of the intervention, blinding of subjects is not possible. whenever possible, healthcare providers will be blinded throughout the perioperative period. However, patients may report being in the study to their providers, which may inadvertently cause unblinding. Outcome adjudicators will be blinded.

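### The sample size for the primary outcome is justified by estimates and intervals, but the analysis table gives that outcome only Fisher's exact test and names no between-arm measure or interval

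*Protocol*

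**What the plan says.** The Sample size estimation section of the Protocol states: "The proposed sample size is 30 (20 intervention, 10 control), balancing cost against precision, as is conventional for a pilot study". It concedes that differences between groups may not be significant, says the sample will give rough estimates of the treatment effects for Aim 1 (cessation) and Aim 4 (complications), and closes by saying that "the point estimates and confidence intervals will provide rough estimates that will be useful in planning a future study". The only formal power statement, "The proposed sample size will have 80% power to detect an effect size of 1.085", concerns the satisfaction score, not quitting.

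The outcome table under Statistical analysis plan gives the primary outcome this row: "Smoking cessation (primary outcome) | Proportion | n/a | Fisher’s exact test". The last column is headed as the hypothesis test. An interval method (exact binomial, 95%) is named in that section only for two feasibility proportions: those ineligible and those declining. Randomization uses "randomly permuted block sizes of 3 or 6 in a 2:1 fashion", which matches 20 v 10.

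**The concern.** For the primary outcome, the only stated reason for the sample size is estimation. The section that fixes the analysis names a test for it, but not the contrast (such as a risk difference) or the interval that the sample-size section relies on. The authors did name interval methods where they considered them, for the feasibility proportions, so the gap falls on the main comparison.

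If the table is followed literally, the headline is likely to be a non-significant p-value. That says little about how large or small the effect could be, which is what a planner of the full trial needs. In addition, Fisher's test at these group sizes works well below its nominal error rate and so gives up some power that another exact test keeps.

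**Working it through.** **Inputs.** 20 ENDD and 10 control patients (Sample size estimation). Control quit rates of 4-65% and differences of 13-76 points, both ranges that the section takes from earlier studies; it picks no planning value. The level comes from "accepting an alpha of 0.05", which is stated for the satisfaction calculation only. Sidedness is not stated for Fisher's test; the table has "Normal: two-sided t-test" for smoking amount only. I therefore assume two-sided 0.05, with all 30 patients analysed.

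**1. The plan's own figure.** Satisfaction score, SD 1.0, 20 v 10. Detectable difference = (1.960 + 0.842) × 1.0 × √(1/10 + 1/20) = 2.802 × 0.3873 = 1.085. The stated 80% power reproduces by the normal approximation (79.996%). A two-sided t-test gives 77.2%. The figure is sound to that approximation, but it does not bear on the primary outcome, for which no power or error rate is stated.

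**2. True size of Fisher's test.** There are 21 × 11 = 231 possible results (x quitters of 20, y of 10). For a common quit rate p,

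size(p) = Σ Bin(x; 20, p) × Bin(y; 10, p), summed over tables with two-sided Fisher p ≤ 0.05.

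| Common quit rate | True size |
| --- | --- |
| 4% | 0.29% |
| 10% | 1.3% |
| 20% | 2.2% |
| 35% | 3.3% |
| 50% | 2.6% |
| 65% | 3.3% |

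The maximum over all rates is 3.26%. The size passes 1% only from a quit rate of about 8%.

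**3. Fisher against Boschloo.** Boschloo's test uses Fisher's p-value as its statistic and takes the worst case over the common quit rate. Two two-sided definitions are in use: (a) order tables by the two-sided Fisher p; (b) double the smaller one-sided Boschloo p. Power is the sum in step 2 with different rates in the two arms.

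| ENDD v control | Fisher | Boschloo (a) | Boschloo (b) |
| --- | --- | --- | --- |
| 60% v 20% | 44.5% | 52.0% | 55.1% |
| 50% v 20% | 27.3% | 30.3% | 34.0% |
| 40% v 20% | 13.1% | 13.7% | 16.4% |
| 33% v 20% | 6.1% | 6.2% | 8.3% |
| Maximum size | 3.26% | 4.1% | 4.3% |

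Both definitions reject every table that Fisher rejects, and a few more.

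**4. What an interval would show.** Take 8/20 v 2/10 as an illustration. The Wilson limits are 0.219 to 0.613 for 8/20 and 0.057 to 0.510 for 2/10. The Newcombe limits are:

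- lower: 0.20 − √[(0.400 − 0.219)² + (0.510 − 0.200)²] = 0.20 − 0.359 = −0.159
- upper: 0.20 + √[(0.613 − 0.400)² + (0.200 − 0.057)²] = 0.20 + 0.257 = +0.457

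The result is +20 points, 95% CI −16 to +46, with Fisher p = 0.42. At 12/20 v 2/10 the difference is +40 points with a Newcombe CI of +2 to +63. Fisher gives p = 0.058; Boschloo gives 0.051 by definition (a) and 0.044 by (b). The definition can decide the result, so it has to be fixed beforehand.

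**The case against.** **The protocol does plan estimates.** A reader might infer from the table that no effect estimate is planned. The document does not support that. The sample-size section promises point estimates and confidence intervals, the row describes the outcome as a proportion, and the difference follows by subtraction. The quoted column lists tests by design. Interval detail is also often left to a separate SAP, which is not shown here. This stands, and it narrows the point to an unnamed contrast and interval method. The mismatch remains, because the protocol's own analysis section fixes a test for its primary outcome and nothing else between arms.

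**Rough estimates are not a planning effect.** A reader might also infer that the full trial will be powered on the pilot's point estimate. The text calls the estimates rough and mentions intervals alongside them. The section on future funding says the full trial will lean towards Aims 2-4. That inference fails.

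**Conservatism is not an error.** A true size below 5% is a known property of a valid exact test, Fisher is a conventional choice here, and the protocol already accepts low power. This stands. The case for Boschloo is an efficiency gain, which depends on the two-sided definition and nearly vanishes at 33% v 20%. It is secondary to naming the estimate and interval.

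**Conclusion.** The point holds as a mismatch between two sections of the Protocol: the sample size for the primary outcome is defended by estimates and intervals, while its row in the analysis table names only Fisher's test. It is not a claim that estimation is absent or that Fisher's test is invalid.

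Fisher's true size is about 0.3-3.3% over the cited 4-65% range. Replacing it with Boschloo raises power by 7.5-10.6 points at 60% v 20% (52.0 or 55.1 less 44.5) and by 3.0-6.7 points at 50% v 20% (30.3 or 34.0 less 27.3), loses no Fisher rejection and stays below 5%. For smaller differences neither test has useful power, which is a further reason to lead with the interval.

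These figures assume two-sided 0.05 and complete data on 20 and 10 patients. The quit rates in the power table, including the 20% control rate, are illustrations, since the protocol chooses none.

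**What to change.** In the Statistical analysis plan table:

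- Make the primary analysis the difference in quit proportions on the day of surgery (ENDD minus control) with a 95% CI by a named method, for example Newcombe. Make any p-value secondary.
- Do the same for the other binary between-arm rows: smoking reduction, unanticipated admission, daily use and non-use of the product, and the 30-day composite.
- If a test is kept, replace Fisher by Boschloo's exact test and state the level, the sidedness and which two-sided definition applies.

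The cost is table wording and a few lines of code, with no extra patients or data. The small downside is a less familiar test whose two-sided definition must be set before the data are seen.

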## Control and intervention groups:

**1) Electronic nicotine delivery device group (ENDD) + referral to the California Smokers' Helpline**

The ENDD group will receive:

i) 6-week supply of disposable "NJOY" ENDDs (e-cigarettes)

-the number of e-cigarettes will be determined by equating the number of e-cigarettes to the number of cigarettes smoked per day (1 pack per day = 2 e-cigarettes per day = 14 e-cigarettes/week)

-veterans will be given detailed instructions for use and also instructed to start with the high nicotine content (4.5%) strength for three weeks, then decrease to the low nicotine content (2.4%) for two weeks, then switch to nicotine-free for the final week

ii) referral to the California Smokers' Helpline

-the California Smokers' Helpline is a telephone helpline offering smoking cessation counselling 7am-9pm weekdays and 9am-5pm weekends. Counselling includes individualized counselling and quit plan development, strategies to prevent relapse, and follow-up calls.

iii) brief advice from the research assistant lasting less than 2 minutes, typically a few sentences such as the following:

“The most important advice I can give you is that quitting smoking is the number one thing you can do for your health. Quitting smoking before surgery may reduce complications around surgery and there’s evidence that the longer you quit before your surgery, the less complications you’ll have. That's why your surgeon and anesthesiologist have recommended that you stop smoking as soon as possible. I encourage you to make use of the resources that have been provided to you to help you quit and to set your quit date for as soon as possible.”

iv) a brochure from the American Society of Anesthesiologists (ASA) about quitting smoking before surgery (available free from the ASA).

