**2) Control group (referral to the California Smokers' Helpline + transdermal nicotine replacement therapy)**

The control group will receive the same counselling as the intervention group, but will receive a prescription for transdermal NRT instead of ENDD:

A prescription for 6 weeks of transdermal nicotine replacement (on-formulary at the VA) in the following doses: For smokers of 10 cigarettes per day or more, a 3-week supply of 21 mg/d, 1-week supply of 14 mg/d, 1-week supply of 7 mg/d, and 1-week of 0mg/d. Smokers of <10 cigarettes per day, 3 weeks of 14 mg/d patches 2 weeks of 7 mg/d patches, and 1-week of 0mg/d.

As with the intervention group, the control group will receive:

i) referral to the California Smokers' Helpline, ii) brief advice lasting less than 2 minutes, iii) a brochure from the ASA about quitting smoking before surgery

Table 1. Summary of study intervention

| **Study intervention** | **Intervention group (ENDD)** | **Control group** |
| --- | --- | --- |
| E-cigarettes (6-weeks) | YES | × |
| Transdermal NRT (6-weeks) | × | YES |
| Referral to the California Smokers' Helpline telephone helpline | YES | YES |
| Brief advice | YES | YES |
| ASA brochure | YES | YES |

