**Secondary outcomes:**

1. Descriptive outcomes of proportion of veterans eligible for inclusion, reasons for exclusion, and proportion of eligible veterans consenting to participate. Acceptability outcomes of satisfaction and use of intervention (any versus continuous) 8-weeks after randomization.

2. Smoking status at 8-weeks after randomization, as confirmed by exhaled CO.

3. Smoking reduction on the day of surgery and at 8-weeks after randomization (defined as 50% or less of baseline cigarettes smoked per day). Dual use of e-cigarettes and conventional cigarettes will also be assessed.

4. Bedside spirometry FEV1 (forced expiratory volume in first second), FVC (forced vital capacity), and cotinine level at 8-weeks after randomization (compared to baseline).

5. Postoperative complications or mortality within 30-days (by telephone self-report + chart review)

6. PACU length-of-stay

7. Hospital length-of-stay

8. Long-term assessment at 6 months - self-reported smoking status, including dual use of e-cigarettes.

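### The product-use item covers six weeks in both arms, but the control regimen has five weeks of active patch and an undefined sixth week, so the everyday-use comparison may tilt towards e-cigarettes

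*Protocol*

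**What the plan says.** The outcome table in the protocol's Statistical analysis plan fixes the wording of a use item asked 8 weeks after randomization: "During the 6-weeks after you entered the study, how often did you use the product you were given (e-cigarettes or patch". There are six response categories, from everyday down to no use. Two summaries are tested by Fisher's exact test: "Proportion that used everyday", and the proportion with no use. The item serves a listed secondary acceptability outcome, "use of intervention (any versus continuous) 8-weeks after randomization".

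The e-cigarette regimen (Control and intervention groups, item 1) is a six-week supply: three weeks at 4.5%, two at 2.4%, and "then switch to nicotine-free for the final week". A device is in hand throughout.

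The control regimen (item 2) has two tiers. For 10 or more cigarettes a day it is three weeks at 21 mg/d, then "1-week supply of 14 mg/d, 1-week supply of 7 mg/d, and 1-week of 0mg/d". For fewer than 10 it is "3 weeks of 14 mg/d patches 2 weeks of 7 mg/d patches, and 1-week of 0mg/d". The same section introduces these as "A prescription for 6 weeks of transdermal nicotine replacement (on-formulary at the VA) in the following doses", and Table 1 lists "Transdermal NRT (6-weeks" beside six weeks of e-cigarettes. The protocol does not say what a control wears, if anything, in the 0 mg/d week.

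**The concern.** The item asks both arms about the same 42 days, but the arms may not have product on the same number of days. If controls wear no patch in week 6, perfect adherence to the patch regimen is not everyday use over the window asked about; its literal answer is the next category down. Perfect adherence to the e-cigarette regimen does count as everyday use. The mismatch can only lower the control figure, so it can only favour e-cigarettes.

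Aim 2 and the Sample size estimation section ask the pilot whether e-cigarettes are more acceptable than patches, and the latter says that point estimates and confidence intervals will inform the full trial. A use estimate that differs between arms because of the question's window, and not because of behaviour, would be a poor input to that judgement.

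**Working it through.** **Days with product.** From the two regimen descriptions:

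- E-cigarettes: 21 + 14 = 35 days with nicotine, plus 7 nicotine-free = 42 of 42.
- Patch, 10 or more cigarettes a day: 21 + 7 + 7 = 35 active days.
- Patch, fewer than 10: 21 + 14 = 35 active days.
- Week 6 patch-free: 35/42 = 83%. Week 6 with a 0 mg patch: 42/42, the same as the e-cigarette arm.

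**Which reading of week 6.** For a patch-free week: in the upper tier only the active steps are described as a supply; in the lower tier only the active steps are described as patches; and the NRT costs in the Budget price 7, 14 and 21 mg patches but no 0 mg patch. For a worn 0 mg patch: the introductory sentence and Table 1 both give six weeks, and the 0 mg week parallels the nicotine-free e-cigarette week. The costing is weak evidence, because it does not follow the schedule: it buys one 2-week supply of 21 mg for a three-week step and counts three 2-week supplies as six weeks. Patch-free is the likelier reading, but it is not proved.

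**Size if week 6 is patch-free.** The protocol gives no expected use rates and no power figure for this item, so two quantities are assumed:

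- a = share of each arm who use product on every day it is supplied (equal in both arms, so there is no true difference);
- k = share of such controls who still answer everyday.

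The everyday proportion is then a in the e-cigarette arm and a × k in the control arm, and the spurious difference is a(1 − k). With the planned 20 and 10 participants, the chance that a two-sided Fisher test gives p < 0.05 was computed by exact enumeration of two independent binomials:

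| k | difference at a = 50% (points) | p < 0.05, a = 30% | p < 0.05, a = 50% | p < 0.05, a = 70% |
| --- | --- | --- | --- | --- |
| 1 | 0 | 3.1% | 2.6% | 3.1% |
| 0.75 | 12.5 | 3.4% | 5.7% | 12.1% |
| 0.5 | 25 | 6.3% | 18.2% | 35.9% |
| 0.25 | 37.5 | 12.2% | 46.5% | 71.5% |
| 0 | 50 | 22.8% | 86.8% | 99.9% |

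Typical tables at a = 50%: near k = 0.5, 10/20 against 2/10 gives p = 0.24 and 10/20 against 3/10 gives p = 0.44. At the extreme k = 0, 10/20 against 0/10 gives p = 0.011.

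**After the change.** Over weeks 1 to 5 both arms have active product on 35 of 35 days under either reading, and a fully adherent participant in either arm can answer everyday. With equal true use the Fisher rejection rate is then 2.2% to 3.1% for true rates from 20% to 80%.

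**The case against.** The strongest reply is that the premise is not shown. The 0 mg week is listed among the doses of a six-week prescription, so a 0 mg patch is a fair reading, and under it nothing tilts. That stands, and is why the point is conditional. It does not remove the ambiguity: week 6 of the control regimen is undefined on any reading.

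Second, even with a patch-free week, a control who wore every patch supplied may well answer everyday, since the item refers to the product given and is recalled two weeks after the regimen ends. That also stands. The high rejection rates in the table need mostly literal answering and substantial daily use, neither of which the protocol supplies. A reader might infer a probable false-positive finding for e-cigarettes; the document does not support that. The harm to expect is a tilted estimate.

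Third, the consequence is small. This is one acceptability item in a 30-person pilot that already warns of non-significant differences, and no decision rule uses it. A reader might infer that the proceed decision is biased. It is not tied to this item: the one powered acceptability measure is the 0–7 satisfaction scale. The satisfaction scale, the no-use proportion, the interviews and the primary outcome are not materially affected. Literal adherent controls would also show up in the most-days category of the raw responses, although the planned tests use only the two extremes.

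Finally, restricting recall to weeks 1 to 5 asks participants at week 8 to separate week 5 from week 6, and loses a little information if 0 mg patches are in fact supplied. Both are real but minor costs.

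**Conclusion.** The point holds in conditional form, as a minor improvement. The protocol fixes the window, the category and the test, and leaves week 6 of the control regimen undefined, so this goes beyond a detail that an analysis plan would settle. If week 6 is patch-free, a fully adherent control (35 of 42 days) scores below a fully adherent e-cigarette user (42 of 42) on a listed secondary acceptability outcome. The spurious difference is a(1 − k): at a = 50% it lies between 0 and 50 percentage points, and is 25 points at k = 0.5. Both a and k are assumptions. If 0 mg patches are supplied, the tilt is zero. It would go too far to say that the regimen and the outcome table contradict each other, because the 0 mg/d week can be read either way. Confidence is medium: the day counts and the direction are firm, the reading of week 6 and the size are not.

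**What to change.** Two changes:

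1. In the outcome table and the 8-week questionnaire, word and score the use item over weeks 1 to 5 after entry in both arms. Keep the six response categories and the Fisher tests.
2. In the control-group regimen, state whether controls wear a 0 mg patch or no patch in week 6.

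Scoring use as a fraction of the days supplied is not an alternative, because the item collects a frequency category and no day count.

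The cost is one line in the questionnaire and its matching table entry, and one line in the regimen. Enrolment, visits, the primary outcome and the satisfaction scale are untouched. The loss is that week-6 use of the nicotine-free e-cigarette leaves the between-arm comparison; it can be reported for that arm alone.
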